Starting from the idea that action cognition and motor imagery deficits are stable alterations in depressed individuals [41–43] we use a rehabilitation type of motor imagery intervention based on principles of rehabilitation of motor imagery for individuals with neurological conditions. To this end, we integrate forward modelling of action and motor imagery [44], remote kinematics (Kinect) and embodied cognition account (action support of mental simulations, [25, 45]. This intervention is a new one that proved efficient in clinical work ([name], [Unpublished protocol]), [46]. There are several steps in the intervention. In the first session, the therapists introduce the *dynamic simulation routine*: how to support mental imagery of activities through gestures, language, and attention. Then, the patients undergo an exergame for 5 to 10 minutes and an “actfulness” exercise focusing on feelings of movement and motor simulation. After the exercise, the participants dynamically imagine a planned activity. In session two, patients are thought to restructure action memories by focusing on movements. Deficient action simulations are rehabilitated by (a) partial movements (they alternate covert with dynamic-partial movements simulations in response to stimuli); (b) linguistic supports (training in gerundival perceptions that is to recognize and name stimuli by actions; for instance, a door is recognized as a door to open; [47]), (c) enhanced perceptual and affective simulations (PETTLEP system, [48]), and (d) episodic memory support (they have to form future memories of *action cores*-last sequence of movement before perception of desired environmental change, correct them by experience, and remember at the end of the day). Thus, it is a rehearsal training that mixes actual and mental practice [49, 50] with augmentation of the motor component of simulations in thinking by enhancing *gestures*, *language*, *and episodic memory* as controls of simulation, and is applied to promote the use of motor simulations in everyday life.

We expect that adding a dynamic imagery intervention will augment the effects of behavioural activation treatment (BA) on severity of depressive symptoms. Second, we investigate whether adding the dynamic imagery intervention to behavioural activation treatment has any effect on secondary outcomes such as anhedonia, apathy, and vividness of imagery. Third, we investigate the moderators and mediators of the effects of the intervention.

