### Proposed sample size

The sample size was established using G*Power and selecting the difference between two independent means. Forty-four participants per arm will be required to obtain a 90% statistical power. This estimation is based on previous studies targeting robust processes in depressed individuals (rumination) and between-treatment effect size of Cohen’s d = 0.7. Assuming a dropout rate of 20%, 55 patients are required in each treatment arm, resulting in a total of 110 participants.

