### Statistical analyses

Multiple imputation methods will be selected to address the missing data. All randomised patients will be included in intention-to-treat analyses (ITT). Per-protocol analysis will be conducted separately. Analyses will be computed with an alpha significance level of 5% and two-tailed analyses. Analyses will be performed using IBM SPSS. Comparisons will be computed at a 5% significance level, and BDI II is the primary outcome variable considered as continuous variables. Differences between groups at the posttest will be analysed with a mixed ANOVA having group as the main effect and group *time as an interaction effect. Subgroup analyses will be conducted for anhedonia, apathy, motor imagery, and rumination. F-statistics and p values will be reported for main and interaction effects. The results will be considered as supporting evidence if the F test of the interaction effect is statistically significant (group*time interaction term). Potential mediators of treatment effects will be analysed exploratorily using Hayes model 4 analyses for the primary (depression severity) and secondary outcomes (anhedonia, and apathy). Hayes model 1 will be used to analyse the moderation. Between group effect sizes will be calculated based on Cohen’s d. Treatment completers will be analysed using per protocol analyses. Participants are considered "remitted" if they no longer fulfil the SCID-5 criteria for major depression episodes.

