## Discussion

The study is the first to evaluate an exergame-augmented dynamic imagery intervention added to behavioural activation treatment. It is expected that adding the exergame-augmented dynamic imagery intervention will increase the acceptability of the treatment and decrease the severity of depression, anhedonia, and apathy. We also expect, based on moderation analyses, that this effect to be more pronounced in participants with difficulties of motor imagery at baseline. We further investigate mediators of the treatment effect on the severity of depression and secondary outcomes.

This study is the first to investigate the added benefit of exergame-augmented dynamic motor imagery intervention to behavioural activation treatment. There is an expected advantage that this intervention will make the treatment more accepted (due to XboxKinect^™^) and will overcome the deficiencies in vividness of imagery and the recruitment of motor networks in imagery. If efficient it may work through different mechanisms than the standard BA treatment.

There are several strengths of the study: (1) it is a theory-driven intervention which could show an efficacy advantage, (2) it includes attractive exergames that may show additional benefits (exergame time may be increased and transformed into physical exercise) (3) we included a clinician administered semi-structured interview (SCID-5-CV), (4) we planned for a mid-treatment assessment to evaluate mechanisms of change. At session six, the participants will complete measures of the mechanisms of change, which will be carried out based on temporal precedence criteria [72], (5) assessors are blinded to participants’ treatment conditions.

There are several limitations of the study: (1) it is not a large scale RCT some limitations being related to the small sample size, (2) as the sample size was determined based on post-treatment differences, moderation and mediation analyses being underpowered, (3) participants with high risk of suicide will be excluded based on a score C-SSRS scale [53], limiting the generalisation of the results to participants with high risk of suicide.

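### The exploratory mediation model assumes a mediator acts equally on outcome in both arms; a group-by-mediator sensitivity analysis would show whether that matters (minor)

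*Protocol article*

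**What the plan says.** All references are to the Protocol article.

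- **Mediation model** (Statistical analyses): "Potential mediators of treatment effects will be analysed exploratorily using Hayes model 4 analyses for the primary (depression severity) and secondary outcomes", the secondary outcomes being anhedonia and apathy.
- **Moderation model** (same section), handled separately: "Hayes model 1 will be used to analyse the moderation". No model combining the two is named.
- **Aim** (Introduction): "Third, we investigate the moderators and mediators of the effects of the intervention".
- **Mechanism** (Discussion): "If efficient it may work through different mechanisms than the standard BA treatment".
- **Timing** (Discussion, listed as a strength): "At session six, the participants will complete measures of the mechanisms of change, which will be carried out based on temporal precedence criteria".
- **Stated limitation** (Discussion): "as the sample size was determined based on post-treatment differences, moderation and mediation analyses being underpowered".

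Two further statements bear on the point. The Introduction reports, from earlier work on imagery interventions, that benefit is confined to people who can picture actions vividly. Recruitment of participants describes the T-RAC arm as receiving the same BA protocol with the imagery component on top, so imagery is trained in that arm only.

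**The concern.** Standard model 4 estimates the effect of group on the mediator (a) and the effect of the mediator on outcome (b), and reports a × b. Its outcome equation has no group-by-mediator term, so b is forced to be equal in the two arms. This is a property of the model the article names, not a detail it leaves open.

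Equal slopes are a natural default for many mediators but less so for imagery. If vividness is linked to benefit where imagery is part of treatment, and only one arm trains imagery, the same gain in vividness need not bring the same fall in depression score in the other arm. Imagery vividness is a likely candidate mediator: it is measured, and the Discussion expects T-RAC to improve it. The article does not list the mediators by name, so this is an inference.

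What is at stake is the interpretation of the third aim. With unequal slopes, a single pooled indirect effect describes neither arm. The stated low power does not cover this, since it concerns precision and a larger sample would leave the blend unchanged. Measuring the mediator before the outcome does not remove it either.

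**Working it through.** **Step 1: reproduce the plan's own figure.** The article gives no figure for mediation, but the arm sizes used below come from its sample size: "Forty-four participants per arm will be required to obtain a 90% statistical power", for d = 0.7. The significance level is stated as: "Analyses will be computed with an alpha significance level of 5% and two-tailed analyses".

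- Normal approximation: 2 × (1.960 + 1.282)² / 0.7² = 42.9, so 43 per arm.
- Noncentral t: 43.87, so 44 per arm, with power 90.1%.
- 20% dropout: 44 / 0.8 = 55 per arm, 110 in total.

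The stated sample size reproduces.

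**Step 2: what model 4 estimates when slopes differ.** Let bC and bT be the mediator-to-outcome slopes in BA and in BA plus T-RAC, and SC and ST the within-arm sums of squares of the mediator. Least squares with group and mediator, but no product term, gives

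b(pooled) = (SC × bC + ST × bT) / (SC + ST).

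The model 4 indirect effect is a × b(pooled). With equal arm sizes and equal mediator variances this is the simple average of a × bC and a × bT. Relative to a × bT, the ratio is (bC + bT) / (2 × bT).

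**Step 3: put numbers in.** The article gives no path values, so all of these are assumptions: a = 0.7, residual SD 1 and, except where stated, mediator SD 1 in each arm. Simulated results are from 3,000 trials per setting at 55 per arm, with Monte Carlo 95% intervals for the indirect effect.

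| bC (BA) | bT (T-RAC) | Model 4 | a × bT | a × bC | Ratio to a × bT, formula | Ratio, simulated |
|---|---|---|---|---|---|---|
| 0 | 0.5 | 0.17 | 0.35 | 0 | 0.50 | 0.50 |
| 0.25 | 0.5 | 0.26 | 0.34 | 0.18 | 0.75 | 0.74 |
| 0.375 | 0.5 | 0.31 | 0.35 | 0.26 | 0.875 | 0.88 |
| 0.5 | 0.5 | 0.35 | 0.35 | 0.35 | 1.00 | 1.00 |

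The three effect columns are simulated means.

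**Step 4: unequal mediator variances.** For slopes 0 and 0.5, let one arm's mediator SD be 1.5 times the other's. The weight on bT is then 2.25 / 3.25 = 0.69 if T-RAC has the larger SD, or 1 / 3.25 = 0.31 if BA has. The simulated ratios are the same: 0.69 and 0.31.

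**Step 5: the reverse case.** With bC = 0.5 and bT = 0, model 4 averages 0.17 and its interval excludes zero in 65% of trials (38% to 80% with the unequal SDs of step 4), against about 5% for a × bT. In this setting a × bC is 0.35. With a = 0, model 4 excludes zero in only 3% to 5% of trials whatever the slopes.

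**Step 6: what a group-by-mediator term can and cannot show.** Power to detect the interaction at 55 per arm is 72% for 0 against 0.5 and 23% for 0.25 against 0.5 (63% and 21% at 44 per arm). The price when slopes are equal at 0.5 is that detection of the indirect effect falls from 95% with model 4 to 89% with the T-RAC-arm slope at 55 per arm, and from 90% to 79% at 44.

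**The case against.** A reader might infer that the article contradicts itself, by announcing that T-RAC may act through other mechanisms and then choosing a model that forbids it. The text does not support that. The sentence just before the mechanism statement speaks of overcoming deficits in imagery vividness and in motor recruitment during imagery. The statement can therefore mean simply that T-RAC moves other mediators than BA does. That is a difference in the a paths, or in which mediator carries the effect, and model 4 can represent it. Nowhere does the article say that a given change in a mediator acts differently by arm. Even the Introduction's remark on vivid imagers concerns who benefits from imagery interventions, not a measured slope.

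A reader might also infer that the indirect effect will be halved, or that T-RAC will be falsely credited with a mechanism. Both are limiting cases under assumed slopes. Halving needs a slope of zero in BA together with equal mediator variances. False credit needs a treatment effect on the mediator, and counts a × bT as the only legitimate target. When slopes differ there are two indirect effects, and in the reverse case the one on the BA slope is truly non-zero. That case also fits the design poorly: T-RAC participants receive the full BA protocol, and the article gives no reason why activation, say, should stop working for them.

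Finally, the analysis is exploratory and admitted to be underpowered, and the full protocol or analysis plan, not shown, may contain such a check.

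These objections remove any claim of contradiction or of a known bias, and they lower the priority. What stands is narrower: the named model imposes equal slopes, the trial's theory gives some reason to doubt this for imagery measures, and the model 4 output alone cannot show whether it holds.

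**Conclusion.** The point holds as a minor, inexpensive improvement. If slopes differ and treatment changes the mediator, model 4 reports a variance-weighted blend of two arm-specific indirect effects. Under the assumed values with equal mediator variances, the shortfall against the T-RAC-slope effect is about 50% in the extreme contrast, 26% and 12% in the milder ones, and nil with equal slopes. These sizes rest on assumed slopes and on choosing the T-RAC-slope effect as the comparator; the article supplies neither. The primary test of group by time on the Beck Depression Inventory-II is not touched. Model 4 is a defensible main exploratory model, so the case is for adding to it, not replacing it.

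**What to change.** Keep model 4. In the Statistical analyses section, add a sensitivity analysis for each mediator in which the outcome model includes a group-by-mediator term. Report the arm-specific slopes and indirect effects with intervals beside the model 4 result, and state which indirect effect is meant: the one on the T-RAC slope, the one on the BA slope, or the pooled blend.

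Add two cautions on interpretation. A non-significant interaction is not evidence of equal slopes, given the power in step 6. A claim about mechanism should not rest on the T-RAC slope alone, which would be estimated from some 44 to 55 people; the pooled and arm-specific results should be read together.

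The cost is a few sentences and one extra term in an exploratory model, using data already to be collected. The downside is wider intervals for the arm-specific estimates and slightly more exploratory output.

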### Patient and public involvement

Participants and the public are not involved in the development of the study design. The intervention was modified based on piloting the procedures with healthy individuals and case studies of patients with depression. Based on the feedback from initial testing, procedures were modified to increase acceptability. Both XboxKinect^™^ exergames and imagery interventions were well received by various clinical and non-clinical populations in previous RCTs. Similarly, behavioural activation treatment is a well-received and efficient treatment of depression. Study results are disseminated through presentations at conferences and publications in major outlets for psychology. Local therapists will be trained to deliver behavioural activation. The public will know about the results available on the website and in the media.

## Discussion

The study is the first to evaluate an exergame-augmented dynamic imagery intervention added to behavioural activation treatment. It is expected that adding the exergame-augmented dynamic imagery intervention will increase the acceptability of the treatment and decrease the severity of depression, anhedonia, and apathy. We also expect, based on moderation analyses, that this effect to be more pronounced in participants with difficulties of motor imagery at baseline. We further investigate mediators of the treatment effect on the severity of depression and secondary outcomes.

This study is the first to investigate the added benefit of exergame-augmented dynamic motor imagery intervention to behavioural activation treatment. There is an expected advantage that this intervention will make the treatment more accepted (due to XboxKinect^™^) and will overcome the deficiencies in vividness of imagery and the recruitment of motor networks in imagery. If efficient it may work through different mechanisms than the standard BA treatment.

There are several strengths of the study: (1) it is a theory-driven intervention which could show an efficacy advantage, (2) it includes attractive exergames that may show additional benefits (exergame time may be increased and transformed into physical exercise) (3) we included a clinician administered semi-structured interview (SCID-5-CV), (4) we planned for a mid-treatment assessment to evaluate mechanisms of change. At session six, the participants will complete measures of the mechanisms of change, which will be carried out based on temporal precedence criteria [72], (5) assessors are blinded to participants’ treatment conditions.

There are several limitations of the study: (1) it is not a large scale RCT some limitations being related to the small sample size, (2) as the sample size was determined based on post-treatment differences, moderation and mediation analyses being underpowered, (3) participants with high risk of suicide will be excluded based on a score C-SSRS scale [53], limiting the generalisation of the results to participants with high risk of suicide.

This study investigates the acceptability, feasibility, and preliminary efficacy of adding an exergame-augmented dynamic imagery rehabilitative intervention to behavioural activation treatment. Thus, an ecological rehabilitative intervention for action cognition is available. This study increases our knowledge of highly available treatments with increased accessibility for individuals with depression.
